#### Secondary outcome measures

Fear of movement or re-injury is measured by the Tampa Scale for Kinesiophobia [26], a 17-item scale to obtain a score for the extent to which a chronic back patient fears (new) physical damage due to physical activity. The Dutch version of this questionnaire has been found sufficient reliable and valid [27,28].

Mental health is measured by the Dutch translation of the 12-item General Health Questionnaire [29,30], assessing problems concerning psychological distress, like depression, sleep deprivation, stress coping, and self confidence. Test-retest reliability of the scale is high in a general population, with reported Cronbach's alpha coefficients between 0.86 and 0.90 [30].

Social health is measured by a subscale of the Impact on Participation and Autonomy Questionnaire [31], focusing on the influence of the disability on social relationships; Cronbach's alpha for this factor is 0.87.

Overall work status is measured by a 4-level item (1 = "currently working full duties and/or able to do all of my regular home duties", 2 = "able to do all work and/or home duties but it causes extra pain", 3 = "on restricted duties at work and/or need help with some of my home duties", 4 = "off work and/or need help with most of my home duties").

Individual back extension strength progression was evaluated using repeated isometric measurements on the lower back training and testing machine. A detailed description of these measurements can be find elsewhere [15].

Patient satisfaction is measured at the end of the treatment program by two 3-level items and one 5-level item, in which the degree of satisfaction with the allocated treatment is assessed: (a) "Were you satisfied with the allocated treatment at the start of the program?" (b) "Has your opinion about the treatment changed during the program?" (c) "How satisfied are you now about the treatment that was given to you?"

### Short- and long-term follow-up

Beside a baseline measurement, follow-up data are gathered at two short-term intervals and two long-term intervals. Short-term follow-up measurements are at 5 and 10 weeks after randomization. Long-term follow-up measurements are at 6 months and one year after the end of the intervention, respectively. At every test moment, participants fill in a compound questionnaire on a stand-alone PC, and they undergo an isometric back strength measurement on the lower back machine. The content of the questionnaire varies per test moment: parts of the questionnaire referring to potential prognostic variables (job characteristics, overall health, and physical activity) are only displayed at baseline, and at 6 and 12 months of follow-up. Figure 1 presents a flow chart of the different phases of the study.

### Blinding

Double blinding or placebo control is virtually impossible in trials that involve treatment modalities like the ones used in this study, since both patient and provider are inevitably aware of the content of the treatment.

Because our physiotherapists are aware of which treatment they provide, there is always the possibility that they may inadvertently convey different expectations to the patients in each treatment program. This could enhance non-specific effects in either of the two groups. Therefore, as mentioned, beliefs and attitude of the physiotherapists towards back treatment in general are evaluated at baseline, as well as at the end of the study period.

Another limitation of trials comparing a relatively new treatment to the usual care is the risk of a potential nocebo effect; i.e. patients might feel disappointed after being allocated to the standard therapy. To minimize this effect, both programs are introduced to the patient as potentially equally effective treatments in restoring back function, with the relative efficacy of both programs as the main focus of the study. Moreover, at baseline patients are informed about the opportunity they have to continue with a treatment modality of their choice (e.g. our training device) after finishing the treatment period. Patient satisfaction with the allocated treatment is measured directly after the treatment period.

Other efforts to achieve a certain level of blinding within patients, physiotherapists, and data researchers, are:

• low back strength training and measurement are done as much as possible by two different physiotherapists;

• an independent data manager collects data from all study locations, and recodes patients and locations to unique codes before handing the database to the researchers.

### Statistics

#### Sample size estimates

We attempt to enroll 200 patients at the four military health centers, i.e. 100 patients per treatment group. According to power calculations (α = 0.05 and 1-β = 80%), this sample size is sufficient to detect a 20% difference in our primary outcome measure Global Perceived Effect, between the BS and UC program. In our beliefs, a 20% difference reflects a clinical relevant change in health status.

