**Methods:**

Besides a baseline measurement, follow-up data are gathered at two short-term intervals (5 and 10 weeks after randomization) and two long-term intervals (6 months and one year after the end of the intervention), respectively. At every test moment, participants fill out a compound questionnaire on a stand-alone PC, and they undergo an isometric back strength measurement on a lower back machine.

Primary outcome measures in this study are: self-assessed degree of complaints and degree of handicap in daily activities due to back pain. In addition, our secondary measurements focus on: fear of movement/(re-) injury, mental and social health perception, individual back extension strength, and satisfaction of the patient with the treatment perceived. Finally, we assess a number of potential prognostic factors: demographic and job characteristics, overall health, the degree of physical activity, and the attitudes and beliefs of the physiotherapist towards chronic low back pain.

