#### Primary outcome measures

Global perceived effect [21] is measured by self-assessment on a 7-point scale (1 = completely recovered, 2 = much improved, 3 = slightly improved, 4 = no change, 5 = slightly worsened, 6 = much worsened, 7 = vastly worsened). We defined scores of 1 and 2 as a clinically important change.

Patient-specific functional status [22] is measured by a questionnaire following a patient-specific approach. At baseline, individual patients select three main complaints, i.e. frequent activities which they perceive as important in their daily life, but which are hampered by their back pain. Patients rate the severity of these three complaints on a 100 mm visual analogue scale at each test moment. The responsiveness of the questionnaire is fairly good, with an area under the ROC-curve of 0.82, and with mediate correlations with the Roland Disability Questionnaire (r = 0.69–0.75) and the Visual Analogue Scale (r = 0.70–0.80) [21].

Low-back specific functional status is measured by the validated Dutch version of the Roland Disability Questionnaire [23,24], a widely used 24-item scale that reflects the functional disability due to LBP. Test-retest reliability of this scale is considered good for three weeks (r = 0.83) and six months (r = 0.72) respectively [25].

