#### Data analysis

Statistical analysis will be performed according to the intention-to-treat principle; i.e. patients will be analyzed in the treatment group to which they were randomly allocated. In addition, a per-protocol analysis will be performed, in which only patients with no major protocol deviations will be analyzed. Comparing these analyses with the results of the intention-to-treat analysis will indicate, to what extend protocol deviations and lack of compliance might have biased the results.

In our analyses, we will compare the size of the effect, if any, of isolated back strengthening and of usual care for the low back on our primary and secondary outcome variables. Further analysis will determine whether several potential prognostic variables will influence the magnitude of the treatment responses, and if subsets of patients can be distinguished that can be indicated as good-/bad-responders to our specific back training. Demographic and clinical characteristics, as well as baseline outcome measures will be summarized by descriptive statistics. Longitudinal multilevel analyses will be used to examine differences in all continuous outcome measures at 5 and 10 weeks after randomization, and 6 and 12 months of follow-up.

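### Three instruments are listed as primary, but the trial is sized on Global Perceived Effect alone at an unnamed visit, so the stated 5% and 80% hold only on a reading the protocol never fixes

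*Protocol article*

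**What the plan says.** **How many primary outcomes.** The abstract uses the plural: "Primary outcome measures in this study are: self-assessed degree of complaints and degree of handicap in daily activities due to back pain". The section Outcome measurements does the same. The section Primary outcome measures then describes three instruments, with no order among them:
- GPE, a 7-point rating on which scores 1 and 2 count as a clinically important change;
- patient-specific functional status, three complaints each rated on a 100 mm scale;
- the Roland questionnaire: "Low-back specific functional status is measured by the validated Dutch version of the Roland Disability Questionnaire".

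**What the trial is sized on.** Sample size estimates gives "α = 0.05 and 1-β = 80" (the last figure in percent) and 200 patients, "i.e. 100 patients per treatment group". It concludes that "this sample size is sufficient to detect a 20% difference in our primary outcome measure Global Perceived Effect, between the BS and UC program". Here the primary measure is singular, and no visit is attached to it.

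**What is analysed.** Data analysis compares the two programmes on the primary and secondary outcomes. It adds: "Longitudinal multilevel analyses will be used to examine differences in all continuous outcome measures at 5 and 10 weeks after randomization". The same sentence goes on to 6 and 12 months. Short- and long-term follow-up has patients complete the questionnaire at every test moment. Only the parts on prognostic factors are said to be confined to certain visits.

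**The concern.** The outcome section has three primary measures of equal rank, and the sample size section has one. The alpha and power describe a single GPE comparison at one unspecified time. The analysis section covers all primary measures and, for the continuous ones, four times. A reader cannot tell which result decides whether the back-strengthening programme is efficacious.

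The Discussion expects the findings to inform decisions on adopting the programme. Without a named deciding comparison, a favourable result on any of the three instruments, at whichever visit it appeared, could be presented as a positive primary outcome. The false-positive risk of such a claim would exceed 5%. If the sponsor instead protected all three measures by dividing alpha, the trial would no longer have its stated 80% power.

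**Working it through.** **Inputs from the document.** Alpha 0.05, power 80%, 100 per arm and a 20% difference in GPE (Sample size estimates). Three primary instruments, and a correlation of 0.69–0.75 between the patient-specific measure and the Roland score (Primary outcome measures). Four follow-up times (Short- and long-term follow-up; Data analysis).

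**Assumptions.** Two-sided testing. The 20% is read as 20 percentage points in the proportion with GPE score 1 or 2. Usual-care success is 30–50%. Correlations of the test statistics are 0.5–0.7 between instruments and 0.3–0.7 between visits. The document gives none of these apart from the one correlation above.

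**1. Reproduce the plan's figure.** For two proportions with pooled variance,

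n per arm = [z(1−α/2)·√(2p̄q̄) + z(1−β)·√(p₁q₁ + p₂q₂)]² / (p₂ − p₁)².

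For 40% against 60%: [1.960 × 0.7071 + 0.8416 × 0.6928]² / 0.04 = (1.386 + 0.583)² / 0.04 = 96.9, so 97 per arm. For 30/50 or 50/70 it is 93. The planned 100 per arm covers each of these, with power 81.2% at 40/60. The sample size is therefore sound for one GPE test.

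**2. False-positive risk if any one primary result could be claimed, each tested at 0.05.** For m independent tests the risk is 1 − 0.95^m. For correlated tests it was simulated (400,000 draws of multivariate-normal test statistics).

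| Comparisons | Independent | Correlated, as assumed |
|---|---|---|
| 3 instruments, one visit | 1 − 0.95³ = 14.3% | about 11–13% |
| 1 instrument, four visits | 1 − 0.95⁴ = 18.5% | about 13–17% |
| 2 continuous instruments × four visits | 1 − 0.95⁸ = 33.7% | about 21–30% |
| 3 instruments × four visits | 1 − 0.95¹² = 46.0% | about 26–39% |

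With correlations as high as 0.8 in both directions, the first, second and last rows fall to about 10%, 11% and 21%. Every row stays above 5%.

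**3. Power if alpha is split over the three instruments.** α = 0.05/3 = 0.0167, so z = 2.394. Power = Φ{[(p₂ − p₁)√n − z·√(2p̄q̄)] / √(p₁q₁ + p₂q₂)}.
- 40% against 60%: (2 − 2.394 × 0.7071) / 0.6928 = 0.443, power 67.1%.
- 30% against 50%: (2 − 2.394 × 0.6928) / 0.6782 = 0.503, power 69.3%. By symmetry, 50% against 70% gives the same.

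Restoring 80% at 40/60 would take 130 per arm.

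**4. If one GPE comparison at one visit is decisive.** Alpha stays at 0.05 and step 1 applies unchanged.

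**The case against.** **The sample size section already singles out GPE.** It does, in the singular. If GPE at one visit is the sole decisive test, 5% and 80% both hold. But that section does not make GPE the only confirmatory outcome, the outcome section does not demote the other two, and the visit stays open even on this reading.

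**The stronger reading: 12 tests and a 46% error rate.** A reader might infer that the plan tests each instrument at each of four visits and that its true error rate is 46%. The document does not support this. The four times are attached only to continuous outcomes. For GPE they are inferred from the questionnaire being given at every test moment. A longitudinal model need not mean a separate 0.05 test at each visit. No section says that any one success suffices, and 46% also needs independence, which is implausible for these measures. Requiring all three measures to succeed would not inflate the error at all. Twelve is therefore an upper count, and the 26–46% is conditional.

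**The stated alpha is not false.** It is an input to a power calculation, and the article makes no claim about error across several outcomes. A reader might also infer that the sample size is wrong. It is not, for the single GPE comparison it describes.

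**Multiplicity detail may sit in a fuller document.** Adjustment mechanics can be left to an analysis plan that is not shown, and their absence is not held against the article. What remains is a conflict within the stated text: three primaries in one section, one in another, and no visit for the comparison on which the trial is sized.

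**Conclusion.** The concern holds as an inconsistency about the primary endpoint. The protocol ranks three instruments equally as primary, sizes the trial on one of them at an unspecified time, and compares groups on all of them. The 5% and 80% are correct for GPE success at one visit as the only deciding test, a rule the article does not state.

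The size depends on what would count as success. If any primary measure could, the false-positive risk is about 11–14% at a single visit, and about 26–46% as the upper count over all instruments and visits. If alpha is shared equally among three measures, power is about 67–69%. These figures rest on the assumed correlations, usual-care success of 30–50%, a 20-point absolute difference and two-sided testing. That the risk exceeds 5% under an any-measure rule does not depend on the particular values tried. The figures do not show that the trial as planned has a 46% error rate.

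**What to change.** Reconcile Primary outcome measures, Sample size estimates and Data analysis before the database is released to the researchers:

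1. Name one confirmatory comparison: the proportion with GPE score 1 or 2 in each arm at one stated visit, two-sided 0.05. GPE is proposed because the trial is sized on it and the success definition already exists.
2. The sponsor chooses the visit. Ten weeks, the end of the programme, is a natural candidate. The document does not rank the visits, however, and its Background criticises earlier studies for lacking long-term results, so a later visit could also be argued.
3. Either test the other two instruments at that visit in a stated fixed order, each only if the preceding test succeeds, or list them as secondary. The order is also the sponsor's choice.
4. Label results at the other visits as supportive.

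The cost is a few lines of text. The other measures and visits lose stand-alone confirmatory status. Alpha, power and 100 per arm stay as stated. Should the sponsor prefer to keep three co-equal primaries with alpha divided, the trial would need resizing, to about 130 per arm at 40% against 60%.

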#### Data analysis

Statistical analysis will be performed according to the intention-to-treat principle; i.e. patients will be analyzed in the treatment group to which they were randomly allocated. In addition, a per-protocol analysis will be performed, in which only patients with no major protocol deviations will be analyzed. Comparing these analyses with the results of the intention-to-treat analysis will indicate, to what extend protocol deviations and lack of compliance might have biased the results.

In our analyses, we will compare the size of the effect, if any, of isolated back strengthening and of usual care for the low back on our primary and secondary outcome variables. Further analysis will determine whether several potential prognostic variables will influence the magnitude of the treatment responses, and if subsets of patients can be distinguished that can be indicated as good-/bad-responders to our specific back training. Demographic and clinical characteristics, as well as baseline outcome measures will be summarized by descriptive statistics. Longitudinal multilevel analyses will be used to examine differences in all continuous outcome measures at 5 and 10 weeks after randomization, and 6 and 12 months of follow-up.

### Supervision of the centers

In order to obtain full commitment from the participating military health centers, as well as to make sure that every center uses the study protocols in the same way, we organize several feedback and feedforward sessions with all participating physiotherapists. In these sessions, we explain different aspects of the trial design, give instructions on the test and training protocols, and answer remaining questions.

After these sessions, we install the required equipment (test/training machine, soft- and hardware) at the four locations. Each center has a practice period of about 8 weeks to become familiar with the instruments, logistics and protocols, by means of ad hoc training and test sessions with non-participating (regular) back patients. Our researchers join these sessions and, if necessary, give correcting feedback during and after a test or training.

After this practice period, each location officially starts with the study. Once every two weeks, our researchers visit the centers to monitor progress in recruitment and data handling, and to observe the execution of test and training sessions.

## Discussion

This article describes the rationale and design of a multicenter randomized controlled trial in which the efficacy of a specific type of lumbar extension training and usual care are compared in patients with nonspecific LBP longer than 4 weeks. A substantial number of trials have been conducted that included lumbar extension training in low back pain patients [4,7,11,12,32,33]. So far, only the study by Risch et al [11] has emphasized a minimal intervention approach comparable to ours, which was, however, conducted in a non-randomized study design.

Our population at risk can be seen as a selected population of mainly male employees, who work in a dynamic organization with a strong culture of physical fitness. We realize that this selection might limit the external validity of the outcomes of this study. However, results of the trial may be extrapolated to other working populations with a more-than-average degree of physical straining job activities, e.g. policemen and firemen on duty or construction workers.

Besides, despite the "fit-and-healthy" image that soldiers have in our society, a large health survey among a cross-section of male military personnel of 30–40 years showed no favorable scores on several cardiovascular and fitness parameters in comparison to other populations of Dutch men [34,35]. In this perspective, the RNLA – with over 30,000 military and civilian employees a major professional organization in the Netherlands – seems to be a good reflection of Dutch society in general with regard to general health parameters.

Moreover, for reasons of homogeneity it might be even an advantage to only have a study population of working men with (probably) moderate low back trouble in this study.

We hope with this trial to give greater insight to caregivers within and outside the RNLA on treatment options for workers in the sub-acute or chronic phase of their LBP. If, for instance, our minimal intervention approach is equally or more effective than the usual care, medical decision makers may consider implementing this treatment modality in the daily practice of the physiotherapist, by weighing the costs (e.g. price and depreciation costs of materials) and benefits (e.g. reduction of treatment time).

## List of abbreviations

RNLA = Royal Netherlands Army

RCT = randomized controlled trial

LBP = low back pain

BS = Back Strength intervention

UC = Usual Care intervention

rep = repetition on back extension machine
